## Power calculation

Power calculation is performed using the free software PS Power and Sample Size Calculations version 3.0.43(41).

### Paired analysis:

We expect a 20 % reduction in HVPG.

Mean HVPG in patients with liver cirrhosis: 17,9 mmHg(39)

DIFF: (17,9 x 0,2) ~3,58 mmHg

Probability of falsely rejecting the null-hypothesis (type 1 error): 0,05 (95% CI)

Standard Deviation equal to 95% of readings: 3,9 mmHg

The paired comparison including 32 rifaximin treated patients will have a power of **0,998** expecting a 20 % (3,1 mmHG) reduction in HVPG.

We expect a 20 % increase in GFR.

Mean GFR in patients with liver cirrhosis and non-refractory ascites: 69 mL/minute(40)

DIFF: (69x 0,2) ~13,8 ml/minute

Probability of falsely rejecting the null-hypothesis (type 1 error): 0,05 (95% CI)

Standard Deviation equal to 95% of readings: 16 ml/minute

The paired comparison including 32 rifaximin treated patients will have a power of **0,996** expecting a 20 % reduction in GFR.

### Independent analysis:

We expect a 20 % reduction in HVPG. Same values as for paired analysis are applied.

Relation between treated and controls: 2:1

We have 32 experimental patients and 16 patients receiving placebo. The HVPG within the subject group was normally distributed with standard deviation 3,9 mmHg. If the true difference in the experimental and control means is 3,1 mmHg, we will be able to reject the null hypothesis that the population means of the experimental and control groups are equal with probability (power) **0,835**.

We expect a 20 % increase in GFR. Same values as for paired analysis are applied.

Relation between treated and controls: 2:1

We have 32 experimental patients and 16 patients receiving placebo. The GFR within the subject group was normally distributed with standard deviation 16 ml/minute. If the true difference in the experimental and control means is 13,8 ml/minute, we will be able to reject the null hypothesis that the population means of the experimental and control groups are equal with probability (power) **0,79**.

We do not expect any changes in patients receiving placebo on any of the outcome measures.

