# Statistics

Statistics are based on an assessment of demography and incidence of liver cirrhosis Child-Pugh B and C in the capital region of Denmark, which will be the inclusion area of patients.

Taking exclusion criteria in to consideration, we have estimated that a realistic inclusion figure will be between 60 and 70 patients. In this group of patients we expect a drop out rate of 20-25 %.

We expect to achieve a reduction in HVPG as well as an increase in glomerular filtration rate (GFR). The smallest clinically relevant difference in measurements are set to 20 %; that is, a 20% reduction in HVPG and a 20% increase in GFR.

Data will be analyzed paired and independently (as changes between individuals and difference between groups).

Parametric and non-parametric analysis will be used, depending on the underlying distribution.

The following power calculation is based on Student t-test, with a paired testing, and a fixed sample size of 32 treated patients.

Evident information on mean values of GFR and HVPG is inconclusive. The following analyses are made on available sources(39;40) and our best estimate.

In consideration of the relatively small population size, we plan no interim analyses.

Therefore, including a dropout rate of minimum 20-25 %, our aim is to include 32 + 6 = 38 patients for treatment and 16 + 3 = 19 patients for placebo. Hence, the following power calculations are done with a fixed sample size of 48 patients, 32 in treatment group, 16 in placebo group.

The trial will be disrupted when we have included enough patients to meet sample size and power.

We plan to perform both intention to treat and pr. Protocol analyses. Hence, all patient data available will be incorporated into analyses.

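### The between-arm HVPG power of 0.835 is stated for a 3.1 mmHg difference but belongs to 3.58 mmHg; at 3.1 mmHg it is 0.72

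*Protocol*

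**What the plan says.** The Statistics section of the protocol sets the smallest clinically relevant differences as "a 20% reduction in HVPG and a 20% increase in GFR". Under Paired analysis the HVPG target is worked out from a published mean, "Mean HVPG in patients with liver cirrhosis: 17,9 mmHg(39", giving "DIFF: (17,9 x 0,2) ~3,58 mmHg". The sentence that closes the paired HVPG calculation then reports a power of 0.998 while "expecting a 20 % (3,1 mmHG) reduction in HVPG".

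The Independent analysis section opens with "We expect a 20 % reduction in HVPG. Same values as for paired analysis are applied". It takes an SD of 3.9 mmHg with 32 rifaximin and 16 placebo patients, and continues: "If the true difference in the experimental and control means is 3,1 mmHg, we will be able to reject the null hypothesis". The power attached to that sentence is 0.835.

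**The concern.** The same 20% reduction appears as two different numbers, 3.58 mmHg and 3.1 mmHg, and the between-arm power is attached to the one that was not derived. A mean of 15.5 mmHg would make 3.1 mmHg a 20% reduction, but no such mean appears in the protocol.

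HVPG is one of two primary outcomes, and this is its only between-arm power figure. The between-arm comparison is the one that uses the placebo control, which the Ethics section justifies as necessary for attributing effects to rifaximin. The Statistics section also makes the end of inclusion depend on having enough patients for the planned sample size and power. Read literally, the protocol claims more than 80% power for an effect that the design would miss more than one time in four.

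**Working it through.** **Inputs**

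- Mean HVPG 17.9 mmHg, target reduction 20%, SD 3.9 mmHg (Paired analysis; the SD is repeated under Independent analysis).
- 32 rifaximin and 16 placebo patients (Independent analysis).
- Type 1 error: "Probability of falsely rejecting the null-hypothesis (type 1 error): 0,05 (95% CI". It is read as two-sided because it is tied to a 95% interval; this reading is tested below.
- Student t-test (Statistics section), with the software named in the Power calculation section.

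**Target difference**

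- 0.20 × 17.9 = 3.58 mmHg.
- 3.1 / 17.9 = 17.3%.
- 3.1 / 0.20 = 15.5 mmHg.

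**Between-arm power**

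Standard error of the difference = 3.9 × √(1/32 + 1/16) = 1.194 mmHg. Degrees of freedom = 32 + 16 − 2 = 46, so the two-sided 5% critical value is 2.013. Power comes from the noncentral t distribution with noncentrality = difference / 1.194.

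| Difference (mmHg) | Noncentrality | Power | Stated |
|---|---|---|---|
| 3.58 | 2.998 | 0.835 | 0.835 |
| 3.1 | 2.596 | 0.720 | 0.835 |

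Solving backwards, the difference that gives a power of 0.835 is 3.579 mmHg. At 3.1 mmHg the shortfall is 0.835 − 0.720 = 0.115.

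**Could another reading rescue 3.1 mmHg?**

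- *One-sided 5% test.* This gives 0.819 at 3.1 mmHg, which is near but not equal to the stated figure. The between-arm calculation for glomerular filtration rate (GFR) rules it out: with a difference of 13.8, an SD of 16 and the same arm sizes, the two-sided power is 0.787 (stated 0.79) and the one-sided power is 0.871.
- *Enrolled rather than completing patients, 38 versus 19.* This gives 0.794 at 3.1 mmHg.
- *Equal allocation of the 48 patients, 24 versus 24.* This gives 0.769 at 3.1 mmHg.
- *A different SD.* It would have to be about 3.38 mmHg instead of 3.9.

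**The paired figures (n = 32, df = 31)**

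Noncentrality = difference / SD × √32. Two methods are shown: the exact noncentral t and the shifted central-t approximation.

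| Paired comparison | Noncentrality | Noncentral t | Shifted central t | Stated |
|---|---|---|---|---|
| HVPG, 3.58 mmHg | 5.19 | 0.999 | 0.998 | 0.998 |
| HVPG, 3.1 mmHg | 4.50 | 0.992 | 0.990 | 0.998 |
| GFR, 13.8 ml/min | 4.88 | 0.997 | 0.996 | 0.996 |

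The shifted central-t approximation reproduces both paired figures, and also gives 0.835 and 0.787 for the two between-arm figures. All four stated powers are therefore recovered when the HVPG difference is 3.58 mmHg, and neither HVPG power is recovered at 3.1 mmHg.

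**Sample size if 3.1 mmHg were intended**

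At 2:1 with an SD of 3.9, 42 + 21 completers give 0.833 and 44 + 22 give 0.850. About 44 + 22 = 66 completers would be needed to reach 0.835, against the planned 48.

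**The case against.** The strongest reply is that this is a misquoted difference and not a miscalculated power. The 20% target is stated repeatedly and multiplied out to 3.58 mmHg, the paired values are said to carry over, and all four powers reproduce with the derived inputs. On that reading the calculation was run at 3.58 mmHg, the 0.835 is right for the protocol's own target, and no sample size, decision rule or analysis changes. The figures of 0.72 and 44 + 22 completers then describe a target the sponsor never had. The trial also calls itself mainly explorative.

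Most of this stands. A leftover or mistyped 3.1 is the likeliest explanation, and the loss of power is conditional on 3.1 mmHg being the real target. The contradiction remains, however. The wrong number appears in both HVPG power statements, once with the 20% label directly attached, and the text alone does not settle which value was intended. HVPG is designated a primary outcome, so its power statement should be correct however exploratory the trial.

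**Conclusion.** The point holds. As written, the between-arm HVPG power is wrong for the difference it is stated for: 0.720 instead of 0.835 at 3.1 mmHg, an overstatement of 11.5 percentage points. The 0.835 belongs to 3.58 mmHg. The paired figure carries the same misquoted difference, but little hangs on it, since power is at least 0.99 either way.

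If 3.58 mmHg is the target, which the evidence favours, the planned 32 + 16 completers are unaffected. If 3.1 mmHg is the target, between-arm power falls below 80%. The result assumes a two-sided 5% test, which the GFR figure supports, and takes 3.9 mmHg as the SD in the way the Independent analysis section does.

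**What to change.** Use one HVPG difference in both the Paired analysis and Independent analysis sections.

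- If the target is 20% of 17.9 mmHg, replace 3.1 with 3.58 mmHg in both places and keep the power of 0.835. The cost is a text correction with no change to the design.
- If 3.1 mmHg is the target, state a between-arm power of 0.72, restate the paired power as about 0.99, drop the 20% label, and either accept the lower power or revisit the sample size (about 44 + 22 completers for 0.835).

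The sponsor should confirm from the power-calculation record which difference was entered.

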# Data management

Data in this trial is retrieved from the patient’s medical records, the patient’s oral statements, laboratory results regarding biochemistry and investigational results. All data regarding this trial will be stored and kept in the electronic case report form that will function as an encrypted database. All data is handled confidential. The CPR number and the two-digit trial number identify patients. Laboratory results and investigational results are manually transferred to the electronic CRF to collect all study data in one database. The entry of data is performed by investigators or study nurse.

This makes it possible to extract data and continue or repeat data analyses if relevant or necessary in the future.

The electronic case report form and database is accessed electronically with personal user ID and password.

Only the principle investigator and sub investigators handling the care and registration of participants and situated at Hvidovre hospital will have encoded access to the electronic CRF and the encrypted database.

At the end of the inclusion period data will be extracted and analysed by primary investigator. Primary analysis will address the primary outcomes of this trial; thereafter analysis of secondary outcome measures will be performed. Data that are collected, but not immediately analysed is stored anonymously and may conclude in later analyses and statements. We aim at publishing all results derived from this trial.

## Missing data

During the trial period missing data is initially sought in the patient’s medical record. If the parameter is not available at the time of primary analysis the registration will be left empty. Primary investigator and sub investigators will pursue the options of repeating biochemistry and blood analyses when this is possible to complete data. Invasive procedures will not be repeated, should data be missing after the patient has completed the trial investigations.

At the end of the trial, all data will be published in an anonymous form.

# Ethics

This study will be conducted according to national legislation on health and ICH-GCP guidelines as mediated by the GCP unit, Copenhagen University Hospital.

The GCP-unit, Copenhagen University Hospital will monitor all aspects of the trial according to GCP guidelines.

The trial will be reported to the Regional Science Ethics Committee of the capital region of Denmark.

Permission from The Danish Data Protection Agency and Danish Medicines Agency will be obtained before initiation of this trial.

Authorities will have full access to data, documents and registration procedures during monitoring, audits and inspections.

## Obtaining consent

Participants will only be recruited through regular outpatient clinics in the capital region of Denmark and performed by the patient’s regular physician. Advertisement or recruitment will not be performed elsewhere.

The patient’s regular physician will inform patients in oral at the patient’s primary hospital.

If the patient indicates interest in the trial, written participant information is handed out (appendix 1,2 and 3). The patient will also be informed that he or she is in title to reflection and can request an extra interview where he or she can be informed in oral. All information will be provided in private consultation rooms, unless the patient wants it elsewhere. Patients with liver cirrhosis are chronically ill and spend some time on outpatient visits and controls. The information procedure is chosen to avoid contacting the patients further and to secure a safe and familiar environment for interview and information.

Contact information on the principle investigator will be provided in oral and in writing. During admission participant information, patients’ rights regarding participation in medical trials and a resume of the protocol in Danish will be available at all times to the patient.

The patient can choose to sign the written consent form at the outpatient clinic with his or hers primary physician.

When written consent is obtained the patient will be enrolled in the trial and referred to Hvidovre Hospital. Written consent forms will be forwarded to principle investigator by fax, in scanned version on email or by registered mail, to ensure that they are in hand when the participant initiates the trial at Hvidovre.

## Patient disadvantages and risks

Participants randomised to rifaximin treatment may experience side effects to medication; Risks and side effects related to medication and placebo are elaborated on p. 18.

All investigations are thoroughly described in appendix 6. Risks and complications related to investigations are elaborated on pp. 14-16.

Participation in this trial requires more than two days extra hospitalisation and an extra outpatient visit, during the 4 weeks of trial course. Moreover, we repeat a whole series of investigations, not all relevant or beneficial for the individual patient at the time of investigation. There are some nuisances and pain related to the investigations, even though we will try to compensate and relieve the participants as much as possible. The patients will, irrespective of their participation in this trial be offered elucidation of their liver cirrhosis with liver vein catheterisation, and we have placed the initial investigations in relation to this admission to hospital, hence to minimize days of hospitalisation.

One third of participants will receive placebo medicine. At present, there is no registered medication, that prevents bacterial translocation from the gut and actively lowers the hepatic venous pressure, and it lacks yet to be proven whether rifaximin has an effect on these parameters. Hence, patients are not withheld proved active medication. All patients continue their regular prescribed medication during the trial period.

Participants randomised to placebo treatment will most likely not experience any differences or improvement in symptoms and events related to their disease.

The use of placebo is considered necessary to secure that observed effects are ascribed to rifaximin with certainty.

## Patient benefits

Participation in this trial contributes to new knowledge about the foundations and scientific background that causes the serious complications to liver cirrhosis, thus enabling us to improve diagnosis and treatment of this disease and its co morbidity.

At the same time participation helps in understanding the possible mechanisms and possibilities of rifaximin in prevention and treatment of liver cirrhosis and its complications.

It is possible that trial participants randomised to rifaximin treatment will experience an improvement in both kidney function and bowel function, with less distress, flatulence or diarrhoea. It is also possible that this group of patients will have fewer complications to their cirrhosis, such as fewer admissions to hospital, fewer infections and a smaller risk of variceal bleeding and SBP.

It is also a possibility, but not certain, that participants randomised to rifaximin will experience improvement in their mental status and their general condition, for example less fatigue, better appetite and more strength.

Overall, we have evaluated benefits and risks of this trial and assessed it to be ethically secure.

# Financing and insurance

## Insurance

Patients participating in this trial will be insured through the national patient insurance. Trial participants are informed of this relation in written information of trial participant’s right, appendix 2. Sponsor and investigators are covered by Hvidovre Hospital’s statutory insurance.

Norgine Denmark is covered by their own product liability insurance that covered faults in medicine.

## Finance and funding

Rifaximin tablets of 550 mg and placebo tablets in the amounts 2520 tablets (180 blister of 14) and 1260 tablets (90 blisters of 14) respectively, equal to treatment of 38 patients with rifaximin and 19 patients with placebo, are delivered by Norgine Denmark free of costs. See appendix for contracts and agreements.

Norgine Denmark is not further involved in the trial and has no influence whatsoever on the design and methods, nor on compilation and publication of results. For business contract see appendix 7.

Norgine Denmark has not provided funding in addition to the above.

Sponsor and principle investigator have invented the overall template of this research project and have taken initiative to execute it. None of the involved researchers have economic interests or affiliations in private firms, funds or similar.

Research results obtained from this trial are of scientific interest entirely. There are no economic or commercial conflicts regarding the investigations.

The salary of primary investigator is partly financed through employment at Department of clinical physiology and nuclear medicine, Hvidovre Hospital and partly through scholarships and funds.

The department of gastroenterology Hvidovre Hospital will undertake expenses regarding extra outpatient visits and admission to hospital for the purpose of participating in this research project.

Additional costs and expenses will be financed through funds. Expenses regarding analyses and investigations will be covered through funds.

At present we have received grants from The medical foundation of Hvidovre Hospital for the treatment of liver diseases (122.000 kr. + 150.000 kr.) and the Research Foundation for the Capital Region of Denmark (1.000.000 kr.), The Research Foundation Hvidovre Hospital (50.000 kr.), Novo Nordisk Foundation (300.000 kr.), Aase og Ejnar Danielsens Fond (200.000 kr.) and Inge og Per Refshalls Fond (32.400 kr.).

Contributions and scholarships are placed on a research account administered by Hvidovre Hospital. Eventual surplus will be used for remuneration of the study nurse affiliated to this trial. If not relevant, scholarships will be repaid to donors.

Trial participants will be reimbursed for their transportation expenses, after State rates and will be offered remuneration for additional time consumption, Dkr 1500,- in relation to this trial.

# Publication

The trial will be registered in the databases [www.clinicaltrials.gov](http://www.clinicaltrials.gov/) and [www.clinicaltrialsregister.eu](http://www.clinicaltrialsregister.eu/).

The study is expected to lead to more than one publication. The results will independent of outcome be sought published in leading journals within medicine (such as Lancet) or in the leading journals within the area of gastroenterology and hepatology (i.a. Gastroenterology or Hepatology).

Principle investigator [name] will be primary or corresponding author on major publications regarding this trial. [name], [name] and [name], who outlined the study design, will be primary, secondary or final authors on publications regarding this study. Participating investigators will be co-authors according to their work and involvement in the trial.

# Implications

If intestinal decontamination with rifaximin alleviates the mechanism leading to decompensation and complications it may potentially have a clinical impact in advanced cirrhosis far beyond preventing recurrent hepatic encephalopathy. The aspects are prevention of spontaneous bacterial peritonitis in patients at risk of this disease, and potentially prophylaxis for patients with biochemical signs of bacterial translocation.

# List of appendices

Appendix 1: Protocol resume in Danish (for Science Ethics Committee)

Appendix 2: Participant information in Danish

Appendix 3: Written consent form in Danish

Appendix 4: Proxy Statement in Danish

Appendix 5: Guidelines for oral participant information in Danish (for Science Ethics

Committee)

Appendix 6: Investigational programme in English

Appendix 7: Contract between Sponsor/investigator and Norgine Denmark in English

Appendix 8: Sponsor/investigator agreement

Appendix 9: Contract between Sponsor/investigator and trial facilities in Danish

Appendix 10: Investigators Brochure, Rifaximin (for Danish Health and Medicines Authority)

Appendix 11: Investigational Medicinal Product Dossier, Rifaximin (for Danish Health and

Medicines Authority)

Appendix 12: Notification of producer (Orientering af fremstiller, for Danish Health and Medicines Authority)

Appendix 13: Example of medicine label (Etiket eksempel, for Danish Health and Medicines Authority)
